# Immediate versus early (24-hours) urinary catheter removal after elective minimally invasive colonic resection: study protocol for a randomized, multicenter, non-inferiority trial

**DOI:** 10.1186/s13063-022-06894-6

**Published:** 2022-11-22

**Keywords:** Colorectal surgery, Laparoscopy, ERAS, Urinary catheter

## Abstract

**Background:**

Enhanced Recovery After Surgery (ERAS) represents the standard of care in colorectal surgery. Among ERAS items, early removal of urinary catheter (UC) is considered a key issue, though adherence to this specific item still varies among centers. UC placement allows for monitoring of post-operative urinary output but relates to an increased risk of urinary tract infection (UTI), reduced mobility, and patient’s discomfort. Several studies investigated the role of early UC removal specifically looking at the rate of acute urinary retention (AUR) but most of them were retrospective, single-center, underpowered, cohort studies. The main purpose of this study is to compare the rate of AUR after immediate (at the end of the surgery) versus early (within 24 h from the completion of surgery) removal of UC in patients undergoing minimally invasive colonic resection (MICR). The secondary outcomes focus on goals that could be positively impacted by the immediate removal of the UC at the end of the surgery. In particular, the rate of UTIs, perception of pain, time-to-return of bowel and physical functions, postoperative complications, and length of hospital stay will be measured.

**Methods:**

This is a prospective, randomized, controlled, two-arm, multi-center, study comparing the rate of AUR after immediate versus early removal of UC in patients undergoing MICR. The investigators hypothesize that immediate UC removal is non-inferior to 24-h UC removal in terms of AUR rate. Randomization is at the patient level and participants are randomized 1:1 to remove their UC either immediately or within 24 h from the completion of surgery. Those eligible for inclusion were patients undergoing any MICR with an anastomosis above the peritoneal reflection. Those patients who need to continue urinary output monitoring after the surgery will be excluded. The number of patients calculated to be enrolled in each group is 108 based on an expected AUR rate of 3% for the 24-h UC removal group and considering acceptable an AUR of 9% for the immediate UC removal group.

**Discussion:**

The demonstration of a non-inferiority of immediate versus 24-h removal of UC would call into question the usefulness of urinary drainage in the setting of MICR.

**Trial registration:**

ClinicalTrials.gov NCT05249192. Prospectively registered on February 21, 2022.

**Supplementary Information:**

The online version contains supplementary material available at 10.1186/s13063-022-06894-6.

## Background

Enhanced Recovery After Surgery (ERAS) represents the standard of care in colorectal surgery mainly because of the proven impact in reducing postoperative morbidity and length of stay (LOS) [1, 2]. Among ERAS items, early removal of urinary catheter (UC) is considered a key item [3], although adherence to this specific item varies among centers [4, 5].

UC allows for continuous post-operative urinary output monitoring and prevents acute urinary retention (AUR) in the immediate postoperative period. On the opposite, UC is associated with an increased risk of urinary tract infection (UTI), reduced mobility, and patient discomfort [1, 6, 7].

Several studies investigated the role of early UC removal in colorectal surgery but cohorts were generally unbalanced, considering both rectal and colonic resections, open and laparoscopic approaches, and different analgesic regimens including epidural analgesia [8–10]. Besides, most of them were retrospective, single-center, cohort studies.

Li et al. retrospectively analyzed 110 patients submitted to open colonic resection for cancer within an ERAS program comparing 80 patients without any perioperative urinary catheter placement vs. 30 patients where UC was placed before the surgery. The AUR rate was 15% when no UC was positioned and 0% when intraoperative UC was used (*p* = 0.034) [11].

Althoff et al. presented their results from 4 groups of patients undergoing either open or minimally invasive colorectal surgery without catheter placement (27 patients), with catheter removed at the end of surgery (249 patients), UC removed within 24 h (214 patients), and more than 24 h after surgery (151 patients). No significant differences in AUR were observed among groups (3.7% vs. 6.8% vs. 4.2% vs. 2.6%; *p*=0.264). At the multivariate logistic regression, only pelvic surgery was found to be an independent risk factor for AUR (*p*=0.008). Patients with prolonged catheterization experienced a longer LOS (*p*=0.001) and a higher rate of UTI (*p*=0.017) [12].

Conti et al. recently published a retrospective series of 227 consecutive patients undergoing laparoscopic colonic resection analyzing the rate of AUR when UC was removed within 24 h vs. later in the hospital admission. Using a propensity score match, 76 patients with early (within 24 h from the completion of surgery) and 76 patients with standard (median, IQR: 2, 2–3 days) UC removal were compared demonstrating an analogous AUR rate (0% vs. 2.6%; *p* = 0.16). In the study group, patients that had their UC removed early also experienced better results in terms of postoperative complications (6.6% vs. 17.1%; *p* = 0.04), withdrawal of post-operative IV fluids (median, IQR: 1, 1–3 days vs. 2.5, 2–4 days; *p* < 0.001), time-to-return to independent walking (median, IQR: 1, 1–2 days vs. 2, 1–2 days; *p* = 0.02), time-to-tolerate oral feeding (median, IQR: 1.5, 1–2.75 days vs. 2, 1–3 days; *p* = 0.02), and LOS (median, IQR: 5, 4–7 days vs. 6, 5–7 days; *p* = 0.01) [13].

### Rationale for the trial

Despite the number of studies analyzing the feasibility and potential advantages of early UC removal after colorectal resection, current literature lacks strong evidence coming from randomized controlled studies with an adequate sample size. The goal of minimally invasive surgery is to minimize the stress of surgery along with the reduction of the number of unnecessary devices placed into patients’ bodies in the postoperative period. The demonstration of non-inferiority of immediate vs. early (within 24 h from surgery) UC removal would allow clinicians to remove another barrier moving towards a stress-free surgical experience for patients.

### Study aims and objectives

The primary aim of this study is to compare the rate of AUR after immediate compared to early (24-h) removal of UC in patients undergoing minimally invasive colonic resection (MICR). The study hypothesis is that immediate UC removal is non-inferior to 24-h UC removal in terms of AUR rate.

The secondary outcomes focus on items that could be positively impacted by the immediate removal of the UC at the end of the surgery. In particular, the rate of UTIs, perception of pain, time-to-return of bowel and physical functions, postoperative complications, and LOS will all be measured.

### Trial design

This is a prospective, randomized, controlled, two-arm, multi-center study evaluating the feasibility of immediate versus early (within 24 h from the completion of surgery) UC removal in the context of MICR. Randomization is at the patient level and participants are randomized 1:1 to undergo immediate *versus* 24-h UC removal.

The protocol purpose is to demonstrate the non-inferiority of immediate compared to 24-h UC removal in terms of AUR. We assume that immediate UC removal is not significantly inferior to 24-h UC removal. Based on the current literature, to test the alternative hypothesis of non-inferiority of immediate UC removal versus 24-h UC removal, the sample size is calculated using the incidence of AUR. Available data show that the AUR rate can be estimated as high as 3% after MICR [14–16].

Occurrence of AUR, need for postoperative UC placement independently from the cause (e.g., AUR, need of re-operative surgery, and need of admission to the intensive care unit), and UTI will be recorded for every patient in the study., Patients will be asked to report about pain according to a numerical rating scale (NRS) at 6, 12, 24, 48, and 72 h after surgery. Return to passive and active mobilization, return to bowel function as well as the ability to tolerate oral diet will be also recorded together with the occurrence of postoperative complications and the length of hospital stay. The study flow diagram and time of collection of outcomes are shown in Figs. 1 and 2.

**Fig. 1 Fig1:**
[figure not shown]
Overview of the trial design

**Fig. 2 Fig2:**
[figure not shown]
Schedule of enrolment, interventions, and assessments. POD, postoperative day; AUR, acute urinary retention; UTI, urinary tract infection; NRS, numerical rating scale

This study is reported in accordance with the Standard Protocol Items: Recommendations for Interventional Trials (SPIRIT) Checklist for clinical trial protocols (Additional file 1).

### Setting

Participants will be recruited and operated on at the Division of General and Hepatobiliary Surgery, University of Verona Hospital Trust; Division of Colon and Rectal Surgery, Humanitas Clinical and Research Hospital; Division of General Surgery, Ravenna Hospital; and the Division of Colon and Rectal Surgery, Faenza Hospital AUSL Romagna. The caseload of colorectal resections for each center is greater than 150 cases per year.

### Study duration

Recruitment of patients will start in February 2022. The planned duration of the study is 16 months.

### Participants

Patients scheduled to undergo elective MICR.

### Inclusion criteria

Age between 18 years and 80 years oldPatients scheduled to undergo minimally invasive resection of the colon under general anesthesiaWillingness to participateCompliance to study purposeWritten informed consent

### Exclusion criteria

Need for an anastomosis below the anterior peritoneal reflectionNeed for a major resection other than colorectalNeed for post-operative intensive care monitoring or intensive care unit (ICU) stayAnesthesia time longer than 300 minPresence of chronic indwelling UCPresence of an entero-vesical fistulaNeed for ureteral stent placement, bladder resection, or repairA previous and unsolved history of AUR or overt voiding dysfunction

### Interventions

#### Anesthesia protocol

General anesthesia will be conducted according to each center protocol following ERAS guidelines [2]. Deep curarization and goal-directed therapy will be adopted in all centers. No spinal or epidural analgesia will be allowed; conversely, transversus abdominis plane (TAP) bloc or local wound infiltration are encouraged. Duration of anesthesia, analgesia regimen and total amount of IV fluids will be registered.

#### Surgical technique

Multiport laparoscopic or robotic surgery as well as single incision laparoscopic surgery (SILS), or natural orifice specimen extraction surgery (NOSES) will be allowed. Site of minilaparotomy for specimen extraction will be decided by each operating surgeon according to her/his usual technique. Similarly, an intra-corporeal or extra-corporeal anastomosis will be performed according to surgeon’s preference. Conversion is defined as the inability to complete all intended steps using a minimally invasive approach. Duration of surgery, blood loss, adopted surgical technique, need for conversion, and site and length of minilaparotomy will be registered.

#### Interventional treatment

Single IV dose of prophylactic antibiotics within 1 h from skin incision will be administered according to local protocols. Foley catheter (14-16F) will be positioned upon induction using an aseptic technique. At the end of surgery, a member of the surgical staff not involved in the operation will instruct the operating surgeon on the timing of UC removal, according to the group of intervention that the subject was assigned. No prophylactic use of medications to prevent acute urinary retention (e.g., Alpha-lithic agents) will be allowed in both groups.

#### Postoperative analgesia and PONV prophylaxis

Intravenous acetaminophen 1000 mg will be administered 3 times a day (every 8 h) from the day of surgery until post-operative day (POD) 3. Ketorolac 30 mg or tramadol 100 mg will be prescribed as rescue analgesics. PONV prophylaxis is based on the intravenous administration of Metoclopramide 10 mg every 8 h from the day of surgery until POD 3. According to ERAS guidelines, post-operative IV fluids should be discontinued on POD1. Any reason for IV fluids administration after POD1 will be recorded together with its amount.

#### Withdrawal

All patients are freely informed to participate in this study and can decide to withdraw from this trial at any time. Any information regarding patients who decide to withdraw from the protocol are excluded from the final analysis.

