### Sample size calculation

The null hypothesis is that the immediate UC removal is significantly inferior to the 24-h UC removal. Based on the current literature, in order to test the alternative hypothesis of non-inferiority of immediate UC removal vs. 24-h UC removal, the sample size is calculated using the incidence of AUR. Available data show that the AUR rate can be estimated as high as 3% after MICR [14–16].

Sample size was calculated based on the following data. Considering an expected AUR rate of 3% (p1) for the 24-h UC removal group, we choose the non-inferiority limit of δ = 6% with δ = p2-p1, considering acceptable a p2 of 9% for the immediate UC removal group. We calculated that 200 patients are required in each group to give 80% power at a 5% significance level. Considering 8% dropout, the total number of patients to be enrolled is 216, 108 per group (Non-Inferiority Tests for the Difference Between Two Proportions, PASS 14)

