### Allocation and sequence generation

Patients satisfying the inclusion criteria and willing to enter the study are randomized to one of the two study arms after signing the informed consent. The randomization is performed in a 1:1 fashion. The allocation to immediate or early UC removal group is achieved by creating a randomization list. The randomization list has been obtained by an online program available at https://www.sealedenvelope.com/simple-randomiser/v1/lists. A common list is created for all participating centers and patients’ allocation communicated by a member of the proposing center to a member of other centers the morning of surgery. The operating surgeon will be blinded to allocation of the patients until the end of surgery.

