### Statistical analysis

Statistical analyses will be performed on an intention-to-treat (ITT) basis using IBM® SPSS® Statistics software version 21.0 (IBM Corporation, Armonk, NY).

An intention-to-treat analysis (ITT) will be used on all randomized subjects and, where appropriate, an imputation method will be established. It will be also performed per-protocol (PP) analysis that will include all subjects who have finished the catheter removal without major deviations from the research protocol. In non-inferiority studies, both ITT and PP analyses are recommended and should support non-inferiority.

The primary endpoint is AUR. Non-inferiority in the main outcome of the immediate UC removal group compared to 24-h UC removal will be evaluated by test for proportions. The non-inferiority of the immediate UC removal group will be accepted if the upper limit of the 95% confidence interval of the difference in proportions is greater than the non-inferiority threshold value of 6%.

The secondary objectives are assessing the benefits in choosing one procedure or the other, immediate UC removal versus 24-h UC removal. Descriptive statistics and plots will be used to compare the two groups taking into account: (1) UTI rate; (2) overall rate of re-catheterization; (3) pain intensity at 6, 12, 24, 48, and 72 h after surgery; (4) time from surgery to resumption of first oral intake (liquid and soft diet), bowel movements (flatus and defecation), mobilization to chair, and walking; (5) rate of overall, general, and surgery-related post-operative complications; (6) length of hospital stay.

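### The withdrawal rule removes randomised patients and their recorded outcomes from the final analysis, which contradicts the intention-to-treat analysis and leaves both analysis sets blind to bias from withdrawals

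*Protocol article*

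**What the plan says.** The Withdrawal section says that patients "can decide to withdraw from this trial at any time" and then: "Any information regarding patients who decide to withdraw from the protocol are excluded from the final analysis". The exclusion is not limited to the PP set, to data after the withdrawal date, or to patients who refuse further use of their data.

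The Statistical analysis section says: "An intention-to-treat analysis (ITT) will be used on all randomized subjects and, where appropriate, an imputation method will be established". It adds a PP analysis of patients without major deviations, and gives the two analyses a joint role: "In non-inferiority studies, both ITT and PP analyses are recommended and should support non-inferiority".

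Under Allocation and sequence generation, patients "are randomized to one of the two study arms after signing the informed consent", and the allocation is passed on the morning of surgery. A withdrawal can therefore come after randomisation, after catheter removal, or after an AUR event has been recorded.

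**The concern.** An analyst cannot apply both rules. A set without the withdrawn randomised patients is not the set of all randomised patients, and imputation has no role for patients whose information has been removed.

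The primary conclusion is at stake. A non-inferiority trial asks for ITT and PP results to agree because each set is open to different biases. Here one group, voluntary withdrawals, is missing from both, so agreement between the two says nothing about bias from that source. Few primary events are expected, so one or two deleted cases can matter. If the choice between the two rules is left until the data are seen, that choice could decide the verdict.

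**Working it through.** **Inputs from the protocol article (Sample size calculation, Statistical analysis)**
- AUR rate in the 24-hour arm, p1: 3%. Margin: 6 percentage points, so p2 = 9% in the immediate arm lies at the margin.
- Enrolment: 216 in total, 108 per group, after 8% dropout.
- Decision: upper limit of the 95% confidence interval for the difference, compared with 6%. The printed rule accepts non-inferiority when the limit is greater than 6%. I read it as below 6%; that wording is a separate matter.

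**Reproducing the enrolment figure**
- n per arm = (1.645 + 0.842)² × 2 × 0.03 × 0.97 / 0.06² = 100 (one-sided 5%, 80% power, true rates equal).
- 100 × 1.08 = 108 per arm, 216 in total, which matches. The sentence giving 200 in each group does not fit this; that too is separate. I use 108 per arm, the denominator when everyone randomised is kept.

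**Scale**
- Expected AUR events at 3%: 108 × 0.03 = 3.2 per arm.
- Planned dropout: 108 × 0.08 = 8.6 per arm. The allowance exceeds the expected number of events.

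**Illustration 1: one data set (event counts assumed)**

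Wald upper limit: U = (p2 − p1) + 1.96 × √[p2(1 − p2)/n2 + p1(1 − p1)/n1]. The 24-hour arm has 3/108 = 2.78%.
- All kept, immediate arm 5/108 = 4.63%: U = 1.85% + 1.96 × 2.57% = 6.9%. Fails.
- One AUR patient deleted, 4/107 = 3.74%: U = 0.96% + 1.96 × 2.42% = 5.7%. Passes.
- Newcombe limits for the same two cases: 7.9% and 6.7%, both failing. A second deletion (3/106) gives 5.5%, which passes.
- Opposite direction: 4/108 against 3/108 gives a Wald limit of 5.65% (passes). Deleting one 24-hour-arm event (2/107) gives 1.83% + 1.96 × 2.24% = 6.2% (fails).

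**Illustration 2: false non-inferiority rate at the margin**

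Assume that a fraction q of immediate-arm AUR cases withdraw and are deleted, and that no one else does. Let X2 ~ Bin(108, 0.09), K given X2 ~ Bin(X2, q), and X1 ~ Bin(108, 0.03). The analysed data are (X2 − K)/(108 − K) against X1/108. The exact probabilities of all outcomes with U below 6% are summed.

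| q | Wald | Newcombe |
|---|---|---|
| 0 | 3.6% | 2.3% |
| 10% | 6.4% | 3.9% |
| 20% | 11.1% | 6.4% |
| 30% | 18.1% | 10.6% |

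At q = 20% the mean number deleted is 108 × 0.09 × 0.20 = 1.9 patients, well inside the dropout allowance.

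**The case against.** Several points can fairly be made for the plan.

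- **AUR need not lead to withdrawal.** The Withdrawal section concerns patients who choose to leave. Immediate removal is a single act at the end of surgery, and re-catheterisation is a recorded outcome, not a withdrawal. A reader might infer that patients with voiding difficulty are the likeliest to withdraw. The document does not say so, and it gives no withdrawal rate by outcome or arm. This stands, so the bias is conditional. It does not rescue the rule: AUR turns on failure to void within 8 hours of removal or on a residual volume above 300 mL, so the outcome will often already be known when a later withdrawal deletes it.
- **ITT and PP do not collapse into one set.** A reader might infer that both become completer analyses. They do not: patients with a major deviation who do not withdraw stay in ITT and leave PP. The safeguard is lost only for voluntary withdrawals.
- **The verdict need not turn on a single event.** With 100 per arm and Wald limits, 3 against 3 events passes (4.7%) and 4 against 3 fails (6.1%). With the 108 enrolled per arm, 4 against 3 passes (5.65%), and with Newcombe limits one deletion from 5/108 does not change the result. The document names no interval method, so the number of deletions needed to change the verdict varies.
- **Consent must be respected.** True, but the sentence covers everyone who withdraws, not only those who refuse use of their data.
- **Imputation details may sit in an analysis plan that is not shown.** True, and their absence is no fault here. The conflict is between two printed sentences.

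**Conclusion.** The contradiction is explicit and needs correction before analysis. As written, withdrawn patients and their recorded outcomes would be missing from both ITT and PP, so the demand that both support non-inferiority gives no protection against bias from withdrawals.

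The size of that bias is unknown. It favours non-inferiority only if AUR-related withdrawal is concentrated in the immediate arm. Under the assumed 20% loss of immediate-arm AUR cases, the false non-inferiority rate roughly triples, whichever of the two interval methods is used. The stronger claim, that the rule will on its own produce a non-inferiority result, is not supported: this is a possibility under stated assumptions, not a prediction.

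**What to change.** Replace the exclusion sentence in the Withdrawal section with wording such as:

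*Patients who withdraw remain in the intention-to-treat set in their randomised arm. Data collected up to withdrawal are used. Data are removed only where the patient revokes consent to their use, and the number of such patients is reported by arm. Missing AUR is handled by a pre-specified imputation method, with a sensitivity analysis over a range of assumptions for the missing outcomes in each arm.*

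Counting every missing immediate-arm outcome as AUR should be only the extreme bound of that range. With 3 observed events per arm and 8 missing immediate-arm outcomes, it would give 11/108 against 3/108 and a Wald upper limit of 7.4% + 1.96 × 3.3% = 13.9%, so failure would be all but built in.

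The cost is a short amendment, a stated missing-data rule and one further analysis. Enrolment stays at 216.
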